# VERSION CONTROL LOG

*The table below provides an overview of the summary of changes from previous version of this protocol. Where no previous version exists there will be no summary of changes on record.*

| **Version number** | **Date** | **Summary of changes** |
| --- | --- | --- |
| 1 |  | N/A |
| 2 | 29/07/2019 | Removal of punch biopsy on second laser treatment |
| 3 | 13/11/2019 | Contact Details: Additional co-PI for the Morriston Hospital and identifying the independent contact person as previously required by REC  2.2.1 Primary endpoints - deletion of some other biomarkers that will not be identified such as SASP, sequencing apoptotic markers, epigenomics  2.2.2 Secondary endpoint - deletion of 2D since the camera to be used is 3D  3.1 Diagrammatic Overview of Study Design (Figure 1)- The 12 month follow-up commences after the 3rd laser treatment and not after the first laser treatment. Relevant sections of the protocol are amended such as section 7.5.6 on 12-month follow-up visit and Appendix A (Study Schedule).  4.3 Inclusion criteria - adding the word symptomatic on item 2  4.4.1 Laser Exclusion criteria - stating the generic name on item 6 and removal of Type 1 Diabetes Mellitus on item 7 since both Type 1 and Type 2 diabetic patients can be treated.  5.1 Identifying participants - added the specific clinic at Morriston hospital where patients will be seen  5.2.1 changing "Additional psychometric group" sub-title to "PROMS Sub-Study" and clarifying how PROMS Sub-study will be delivered alongside the SMOOTH study.  6.2.1 Control Area - clarifying that patients may opt to undergo laser treatment after the trial is completed  6.2.2 Treatment Area - Specifying the laser settings  7.1.1 Risk - Correcting the period when the expected risk will be resolved  7.3.3.1 Providing additional details on how tissue samples will be handled and stored  7.3.5.1 DSM II is replaced by DSM III as this is the latest available device- Providing additional details about the devices and removing the additional requirement to blanch scars before measurement; blanching scar is not necessary for this study  7.3.5.2 Additional clarification on the use of the device and to include density measurement.  7.4.1 Laboratory assessment - added statement on how biopsies will be handled and stored  7.4.1.1 Minor correction (typo error) on the location where biopsies will be taken.  7.4.1.2 Analysis of blood - changing the volume of serum and plasma to be collected but the total volume of 10mls remain. Clarifying how plasma will be processed.  8.3.1 Added a paragraph on the sample size for the PROMS Sub-study and justifying the significance for the required sample size  10. Amending the funding source details. Insurance was amended as per recommendation of UHB R&D Head of Governance.  12. Archive Plan was revised in accordance with the UHBFT Research Archiving Policy. |
| 4 | 14/02/2020 | 4.4 Exclusion criteria: reducing the timepoint from concurrent invasive scar treatments from 6 months to 3 months as long as it is not on the same area identified for the study.  6.2. Treatment Area: Increased upper limit for laser energy setting to 20mJ; adding statement on carrying out laser treatment on other sites in addition to the randomised scar  7.4.1.2 Analysis of Blood: Increase blood sample volume from 10 mls to 15mls for Morriston Hospital in Swansea due to processing capability of their blood analyser. |
| 4.1 | 15/10/2020 | 7.4.1 The UoB laboratory will initially process the bloods and run a rapid testing for COVID-19 as a safety measure before they proceed in processing bloods for research. UoB lab is currently processing confirmed COVID-ve bloods. If the blood results turn out COVID+ve, the blood samples will be discarded in accordance with the Trust policy in disposing biological samples.  APPENDIX A. Footnote 8 - additional 1 ml blood green top lithium heparin for COVID-19 testing. |
| 4.2 | 23/06/2021 | 6.2 Laser settings; no additional laser treatment will be done on other areas on the duration of the study. (added in version 6.0, classed as substantial amendment) |
| 5.0 | 06/07/2021 | Moving forward the final follow-up time point from 12 months after last laser treatment to 6 months; amended the study outline, study schedule and other relevant sections of the study accordingly. |
| 6.0 | 26/07/2021 | 6.2.2 Amended the laser settings to make it less painful for the patient; no additional laser treatment will be done on other areas outside the randomised scars throughout the study period.  Updated the key study contacts list and details |
| 6.1 | 15/07/2022 | Correction oftypographical errors and addition of current research staff |

# LIST OF ABBREVIATIONS & DEFINITIONS

| **Abbreviation** | **Definition** |
| --- | --- |
| AE | Adverse Event |
| BBSIP | Brisbane Burn Scar Impact Profile |
| CASEVAC | The Casualty Evacuation Club |
| CO_2_ | Carbon Dioxide |
| CTT | Classical Test Theory |
| eCRF | Electronic Case Report Form |
| GCP | Good Clinical Practice |
| KTP | Key Performance Indicator |
| PIL | Patient Information Leaflet |
| POSAS | Patient and Observer Scar Assessment Scale |
| PROM | Patient Reported Outcome Measures |
| QEHB | Queen Elizabeth Hospital Birmingham |
| SAE | Serious Adverse Event |
| SOP | Standard Operating Procedure |
| TBSA | Total Body Surface Area |
| UHB | University Hospital Birmingham |
| UoB | University of Birmingham |
| VSS | Vancouver Scar Score |
| 3D | Three Dimensional |

# BACKGROUND INFORMATION

Burn injury is the fourth most common type of trauma after road traffic accidents, falls and interpersonal intentional injury. In 2004 it was estimated that worldwide 11 million people suffered fire-related burn injury with 265,000 deaths annually. Burns are also one of the leading causes of disability-adjusted life-years lost. Crucially, up to 90% of the patients who survive a burn injury suffer significant scarring, with hypertrophic scars predominating.

Burn care during the last 30 years has seen a step change in survival and this increased survival has been paralleled by improved acute care and durable wound cover resulting in less deformity and scarring. However, there remains an urgent need for improvements in post-burn scar assessment, management and the treatment of historic scars. Gangemi *et al* in a comprehensive review of 703 burn survivors’ records identified the key risk factors for post-burn hypertrophic scarring (1).

These factors included being a young person, female, having dark skin, sustaining a severe burn, number of surgical procedures performed to achieve wound cover, site on the body where the burn occurred and time to wound healing. How these factors influence the treatment of established scars remains poorly understood.

Post burn hypertrophic scarring is typically treated non-invasively with the use of moisturiser, massage, pressure garments, silicone or these modalities in various combinations. A survey of 19 paediatric burn services in the UK showed that 18 services routinely use pressure garments for prevention of hypertrophic scarring following burn injury. More recently injection into the scar of steroids or anti-neoplastic drugs such as Fluorouracil, Bleomycin and Interferon have come into use. Other commonly used drugs include verapamil and botulinum toxin type-A, which have been reported to be beneficial if injected either alone or in combination with steroids.

Laser therapy for treating hypertrophic scarring is a relatively new concept started in the 1980s, being used initially to treat port-wine stains and remove decorative tattooing. Although its use is becoming more widespread for the reduction of established scars its efficacy and mechanism of action remain to be established.

Three main methodological variants of laser therapy have been developed over the years to treat specific aspects of established scars: Pulsed dye lasers, Q-switched Nd:YAG lasers and Fractional lasers. Pulsed dye laser therapy was used to reduce scar vascularity by inducing disruption of the targeted capillaries. This method was also reported to reduce itch. Nd:YAG lasers emit light in the infra-red range, typically with a wavelength of 1064nm and have deeper tissue penetration. They have a range of applications including facial hair and nevus removal.

Fractionated CO2 laser therapy was introduced by Manstein et al in 2004 and essentially bridges the gap between the ablative and non-ablative laser techniques (2). Ablative laser treatments work mainly on the epidermis and non-ablative treatments work solely on dermal collagen, fractional laser treatment works at both the epidermal and dermal layers of the skin making it suitable for treating several aspects of hypertrophic scarring.

Twelve RCTs of laser therapy for the treatment of hypertrophic scars, involving 592 patients, were considered recently in a systematic review (3). Although 11 out of 12 of these trials reported a positive effect of the therapy the review concluded there was insufficient evidence of the clinical effectiveness of laser therapy. This was largely due to variations in the laser therapy used, the scar assessment methods selected and poor study design with a high level of bias. Currently there are 3 RCTs open in Canada and one in the US, this promising new therapy thus remains to have its clinical efficacy in scar management proven.

We suggest that improved understanding of the mechanisms that mediate scar reduction with laser treatment, combined with standardised assessment of scarring and rigorous RCT design, will enable better design of laser treatment regimens and thus benefit those living with hypertrophic scarring.

# STUDY OBJECTIVES

## Objectives

- - 1. **Primary Objectives**

To assess the kinetics of the response to fractionated CO_2_ laser therapy in hypertrophic scars, in particular to test the hypothesis that a positive effect on the scar (assessed through objective and subjective measures) is associated with reduced number of myofibroblasts and the increased presence of senescent skin cells.

- - 1. **Secondary Objectives**

To determine associations between the various cellular and molecular biomarkers and reduction in scarring post laser therapy.

To evaluate the extent to which the use of Brisbane Burn Scar Impact Profile (BBSIP) is a sound psychometric measure of improvements in scarring and the impact on participant’s quality of life as a result of laser treatment.

## 2.2 Study Endpoints

**2.2.1 Primary endpoints**

The primary endpoint is to assess the effect of the ablative carbon dioxide laser therapy via histological assessment of the hypertrophic scarring and in particular using novel methodology to detect the number of senescent cells and the subpopulation of fibroblast 6 months after the third laser treatment.

Scars will be assessed histologically (5mm punch biopsy) to assess dermal and epidermal thickness, collagen structure and orientation, elastin density and structure. Immunostaining will examine possible scar biomarker, proportion of senescent cells and the proportion and sub-population of fibroblasts following treatment.

To identify novel markers associated with scarring and tissue regenerative capabilities such as markers of cellular senescence and DNA damage, for example p16 and ɣH2Ax and other biomarkers including: micro RNAs, TGF-beta, decorin, VAP-1, MMPs, PDGF, adiponectin, etc.

To identify expressions and markers both in blood and tissue samples that influence scar formation, wound healing and variables of scar behaviour in response to CO_2_ laser therapy. This will include; pro and anti-inflammatory cytokines, scar biomarkers and markers of cellular senescence, for example mmp.

**2.2.2 Secondary endpoints**

The secondary endpoints include: subjective (BBSIP, POSAS and mVSS) scores and objective assessment of the areas of interest on Months 3, 6 and 12 after first laser treatment. Objective assessment includes; 3D (Vectra H1) photography, scar thickness and density using Ultrasound (Derma scan cortex Denmark), pliability (Cutometer) and scar colour and pigmentation using DSM Colorimeter .

# STUDY DESIGN

**3.1** **Methodology**

This is a multicentre intra-patient randomised controlled longitudinal observational cohort study, with parallel assignment, single blinded clinical trial to test the effect of ablative fractionated CO_2_ laser on hypertrophic scarring. Two anatomically comparable and independent scars would be selected per subject and randomly allocated to receive either fractioned CO_2_ laser therapy or standard care. An independent assessor will be blinded to the intervention and the control scars sites.

The study will collect quantitative data through tissue and blood samples to assess the cellular and molecular biomarkers response to laser therapy and qualitative data using a series of patient reported outcome measures (PROMs) and scar assessments. Scars will be subjectively assessed using the standard of care scar assessments; Modified Vancouver Scar Scale (mVSS), Patient and Observer Scar Assessment Scale (POSAS)*,* Brisbane Burn Scar Impact Profile (BBSIP). Scars will also be objectively assessed using 3D Vectra Photography for scar site identification, high resolution ultrasound for thickness, Cutometer^®^ for elasticity and colour using DSMII Colorimeter® camera.

As part of the evaluation of the impact of laser treatment on patients’ quality of life a PROMS validation study will be carried out to evaluate if the BBSIP is a useful tool for evaluating the impact of laser therapy on scar tissue and quality of life.

PROMs describe how the patient is functioning or feeling without input from clinical staff (17) providing a unique perspective of patients’ lived experience of the disease as not all symptoms or impacts are obvious to clinicians (18). In order for PROMs to be effective in clinical trials and practice, they have to capture information on domains that matter to the patient (17).

A previous study carried out in Birmingham (13) identified that there were a number of important domains for patients with burn injuries and these were applicable when evaluating relevant interventions. These include: scarring, movement and function, scar sensation, psychological distress, body image and confidence, engagement in activities, treatment burden and impact on relationships.

The study also identified that only two measures had been developed with patient input, in line with FDA recommendations, and only one that was scar specific. The Brisbane Burn Scar Impact Profile (BBSIP) will be used in this study to evaluate its psychometric properties in patients receiving laser therapy. The tool will be validated in this population using Classical Test Theory (CTT) and Rasch Analysis, alongside a range of questions to establish the ability of the PROM to differentiate between groups e.g. improved scar tissue, no change or worse scarring and clinical data.

BBSIP data will be collected in clinics as illustrated in the diagram below (Figure 1), and patients will be given the option to complete a paper and pencil version of the measure or an online version using smart survey. Participants will also be asked to sign a consent to contact form to enable a member of the CPROR research team to analyse their data and have access to information from the demographic questionnaire for use in the psychometric analysis.

Participants to the study will be recruited at the outpatient clinics from the Queen Elizabeth Hospital Birmingham and the Morriston Hospital, Swansea.

Patients deemed suitable for the research trial and who meet the inclusion and exclusion criteria will be assessed for capacity before proceeding with the informed consent process.

**Diagrammatic Overview of Study Design (Figure 1)**

1. **STUDY POPULATION**

## Number of Participants

A total of sixty (60) participants will be recruited to the study over the period of 2 years. Civilian patients will be recruited from the recently established Advanced Scar Management clinic at University Hospital Birmingham and The Welsh Centre for Burns and Plastic Surgery, Morriston Hospital, Swansea. Veterans will be recruited in collaboration with the CASEVAC Club volunteers.

- 1. **Expected Duration of Study**

We anticipate that the recruitment and follow up of 60 patients across both sites will be 2 years or after the 6-month follow-up of the last patient.

- 1. **Inclusion Criteria**

1. Adult patients aged ≥ 16years
2. Patient with symptomatic hypertrophic scarring as a result of deep dermal or full thickness burns/trauma.
3. Trauma or Burn sustained more than 12 months prior to recruitment.
4. Treatment area to be ≥25cm^2^ confluent scarring with a comparable control scar on limb or trunk

## 4.4 General Exclusion Criteria

1. Patients under 16 years of age
2. Previous laser therapy treatment to the study site
3. The use of recent (within 3 months) or concurrent invasive scar treatments, including intra-lesional pharmaceuticals, micro needling or other laser modalities (e.g. Pulse-dye.) on the study site.
4. Known allergy or contraindication to EMLA™ 5% Cream (Lidocaine 2.5% and Prilocaine 2.5%), Dermol 500^TM^ (Benzalkonium Chloride 0.1%; Chlorhexidine Dihydrochloride 0.1%; Liquid Paraffin 2.5%; Isopropyl Myristate 2.5%) or 50:50 ointment (White Soft Paraffin Liquid Paraffin %w/w 50 50.)
5. Patients with Fitzpatrick skin type of 5-6 due to nature of the skin

(The concurrent use of pressure garments, emollient application and scar massage will not exclude enrolment to this study.)

**4.4.1** **Laser Treatment Exclusion Criteria**

1. The presence of acute infection at the proposed treatment site
2. Pregnancy or lactation
3. Patients with poorly controlled Diabetes mellitus HbA1C >9% or 75mmol/mol within last 3 months)
4. Patients experiencing acute exacerbation of Chronic skin diseases e.g. psoriasis or eczema
5. Immunosuppression (HIV, drugs with immunosuppressive effect)
6. Use of Isotretinoin (Roaccutane) at any time within the last 6 months
7. Autoimmune disorders in active stage (for example: 1. Localised: Addison’s, Grave’s and Crohn’s Disease, 2. Systemic:Rheumatoid Arthritis, Multiple Sclerosis, Lupus and Scleroderma).
8. Known history of keloid scarring
9. **PARTICIPANT SELECTION AND ENROLMENT**

## Identifying Participants

Patients will be identified through the Advanced Scar Management clinic, burns and scar therapist outpatient clinics at QEHB and consultants/therapy led clinics at Morriston Hospital, Swansea. Patients may be approached in person by a member of the research team or via telephone during which a brief explanation of the trial will be given.

If the patient agreed, a Patient Information Leaflet (PIL) will be sent by mail or given to the patient.

## Consenting Participants

Written informed consent will be obtained from all subjects before the start of the study related procedure. The research team will assess patient’s eligibility for each treatment intervention, i.e., first, second and third laser treatment, and re-confirm patient’s consent if they agree to continue with the treatment in each time point.

**5.2.1** **PROMS Sub-Study**

Patients attending routine clinical appointments will be asked if they are willing to complete copies of the BBSIP and POSAS plus a consent form and demographic questionnaire to enable psychometric validation of the PROMs. Inclusion criteria will be any patients with sufficient understanding of written English to complete a PROM. Exclusion criteria will be patients with insufficient written English to complete PROMs. Data will be collected over a two-year period in line with the laser study data collection time points. Patients recruited for the SMOOTH study will not be taking part in the PROMS sub-study since the same data will be collected in the SMOOTH study. SMOOTH patients will only be asked to sign one consent form to take part in the study and will complete the PROMs as part of the SMOOTH study.

The PROMS PIS and validation consent form will be used to recruit additional patients who are not part of the SMOOTH study to test the psychometric validity of the BBSIP and POSAS. As only 60 patients will be recruited to the SMOOTH study and this is not sufficient to test the psychometric validity of the PROMs being used. The sub-study will be carried out in routine clinics alongside the SMOOTH study. Data will be collected at two time points and patients will be asked to complete the known groups PROM validation questionnaire at the second time point. This allows the investigators to see if changes captured by the PROMs reflect participants perceptions of change in their scar tissue.

The investigators have both ethical and legal responsibility to ensure that each subject being considered for inclusion in this study is given a full explanation of the protocol and has demonstrated their understanding. This shall be documented on written informed consent forms

An ethically approved written informed consent will be signed and dated by: the subject (or the subject’s legally authorized representative), the individual obtaining consent, and by any other parties required by the ethics committee. This will be completed after the appropriate and essential information has been provided to the participant) and has been fully explained by the investigator (or designee), and it is felt that the participant (or the participants’s legally authorized representative) understands the implications of participating in the study.

The subject (or the subject’s legally authorized representative) shall be given a copy of the signed informed consent form, the original copy shall be kept in the investigator site file at the study centre. A second copy will be filed in the subject’s medical record.

## Screening for Eligibility

Subjects who are deemed suitable for the trial would be identified at Outpatients burn and/or trauma clinic at Queen Elizabeth Hospital Birmingham, Morriston Hospital in Swansea and among the CASEVAC Club members. The research team will approach the participants for screening to ensure that they meet the inclusion and exclusion criteria.

## Randomisation

**5.4.1 Randomisation Procedures**

Each patient will have their own control scar in an anatomically comparable site either on the trunk or limbs. Allocation of scar treatment will be performed using randomisation. Two comparable anatomically scarred areas > 25 cm^2^ on trunk, arms or legs will be identified on the same patient and will be described as location A and location B on the body map. The patient’s identified scar site, A and B, will be randomised on a 1:1 basis to either the standard of care or laser treatment as shown in Table 1.

**5.4.2 Treatment Allocation**

A randomisation list (Table 1) will be prepared before the start of the study and will be implemented using a computer-based randomisation system developed at UHBFT . Once randomised, the treatment allocation will be as follow:

**Table 1.** Options for assignment of study areas

| **Option** | **Treatment allocation for Location A** | **Treatment allocation for Location B** |
| --- | --- | --- |
| Option 1 | Laser Treatment | Standard of care |
| Option 2 | Standard of Care | Laser |

**5.4.3** **Blinding**

Scar assessment will be performed by an independent and experienced assessor in scar management and treatment. This health care professional or scar assessor, in addition to the data analysts will be blinded to the anatomical site (treatment area) receiving laser treatment compared to the non-laser treated scar (control area).

## Removal of Patients from Therapy or Assessment

Subjects may withdraw or be withdrawn from the study at any time.

Patients may be withdrawn from the study if an incidence occurs that renders them unable to continue with the study. For example:

- Patients not able to complete all Laser Therapy Sessions as planned
- Adverse reaction to Laser Therapy
- Pregnancy

The reason for discontinuation will be collected and recorded in the electronic case report form (eCRF). Any data collected at the time of withdrawal may still be included in the data analysis, unless the participant specifically withdraws their consent. Patients will be asked to clarify this at the point of withdrawal.

1. **STUDY TREATMENTS**
   1. **Treatment Schedule/Plan**

Three laser treatment time points will occur at 3 months intervals post recruitment D1, M3 (+/- 30 days) and M6 (+/- 30 days). Scar assessment for both the treatment and the control areas will be performed and recorded prior to randomisation and before each laser treatment. The control site would be treated as per standard of care and if the study subject desire laser therapy for this area, this would be treated on the 6^th^month follow-up after study completion. All study visits are aligned with standard of care treatments and no additional follow up visits would be expected.

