**7.2.3 Pregnancy**

Participants who become pregnant during the trial will no longer be eligible for laser treatment but can continue for follow up if they wish to do so. The patient will continue to receive standard of care.

Pregnancy will be screened but will not be routinely tested during this study.

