## Statistical Analysis

The primary comparison groups will be the scar sections randomised to (control group) versus those randomised to treatment with laser therapy (experimental group). Outcome data will be collected at pre-laser, 3 weeks post the first and third treatments and 12 month

s post third treatment.

All analysis will be based on the intention to treat principle, i.e. all scars will be analysed in the treatment group to which they were randomised irrespective of compliance with the allocated treatment or other protocol deviation. The data analysis for this pilot trial will be descriptive and mainly focus on confidence interval estimation, with no formal hypothesis testing performed.

Dichotomous feasibility measures, like the recruitment and retention rates, including completeness of data will be reported as numbers and percentages. These values will be summarised across participants or treatment groups as appropriate.

Given this study is a pilot, the data will help inform the selection of the most appropriate primary outcome measure for a larger RCT and provide data to estimate the sample size required for the main RCT.

Analysis methods will be chosen according to the data type; 1. Continuous endpoints (e.g. VSS total score): These data will be summarised using means and standard deviations, with differences in means with 95% confidence intervals reported. Longitudinal plots of the data over time will also be constructed for visual presentation of the data. 2. Categorical (dichotomous) endpoints (e.g. rates of improvement in scar domains): The number and percentages of participants/scars experiencing the event will be summarised across and between groups.

As this is a randomised study, there are no priori subgroup analyses specified.

Every attempt will be made to collect full follow-up data on all study participants with the anticipation that missing data will be minimal. The assessment of missing data is an outcome measure of this study.

If a suitable primary outcome is identified during the pilot trial, the level of missing data will form one component of the assessment of feasibility for a future trial. As this is a pilot trial, no formal sensitivity analysis will be conducted.

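### Section 5.5 lets participants be withdrawn from the study, not only from laser, and the final visit hangs on the third laser; this undermines the intention-to-treat statement and can leave a completers' comparison

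*Protocol*

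**What the plan says.** **Withdrawal (Protocol 5.5).** The rule is permissive and conditional: "Patients may be withdrawn from the study if an incidence occurs that renders them unable to continue with the study". The three examples are "Patients not able to complete all Laser Therapy Sessions as planned", "Adverse reaction to Laser Therapy" and pregnancy. The heading mentions both therapy and assessment, but the text describes one action only, withdrawal from the study. On data it says: "Any data collected at the time of withdrawal may still be included in the data analysis, unless the participant specifically withdraws their consent". It describes no collection after withdrawal. The reason for discontinuation goes into the eCRF.

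**Analysis (8.2).** Intention to treat is promised: "all scars will be analysed in the treatment group to which they were randomised irrespective of compliance". The same section aims for full follow-up of everyone, plans no formal sensitivity analysis, and describes a descriptive pilot without hypothesis tests. Retention and completeness of data are among its outcomes.

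**Pregnancy (7.2.3).** Participants who become pregnant "will no longer be eligible for laser treatment but can continue for follow up if they wish to do so".

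**Timing (2.2.1, 7.5.6, Appendix A).** The primary endpoint is histology "6 months after the third laser treatment", and the final visit has the same anchor with a window of 30 days either way. Section 2.2.2 instead counts the secondary endpoints from the first laser, at Months 3, 6 and 12.

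**Biopsies (7.5.1 to 7.5.6, Appendix A).** The control scar is sampled at baseline and at the final visit. The Day 22 biopsy and the one before the third laser are from the laser scar only.

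**The concern.** Failing to complete the laser course is non-compliance with the allocated treatment. Section 8.2 says such scars stay in the analysis, while 5.5 allows the participant to be taken out of the study for it. An intention-to-treat analysis can use only outcomes that were collected, so the withdrawal rule decides whether the promise can be kept.

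The scar comparison is within participants, so a withdrawn participant takes both scars out of later assessments. That does not protect the comparison if removal depends on what happened to the laser scar.

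At stake are the estimates that 8.2 wants to carry forward to a larger trial (choice of primary outcome and sample size) and the retention rate, which would count removals that the protocol itself permits as loss.

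**Working it through.** **1. The plan's own retention figure.** Section 8.1.1 gives a maximum 95% confidence interval width of 25% for retention with 60 participants. The width is 2 × 1.96 × √(0.5 × 0.5 / 60) = 0.253, so the figure reproduces. With the 20% loss allowed for, 60 × 0.8 = 48 participants remain and 12 do not.

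**2. What a participant without a third laser contributes.**

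| Time | Laser-scar biopsy | Control-scar biopsy | Scar scales and devices |
| --- | --- | --- | --- |
| Baseline | yes | yes | yes |
| Day 22 | yes | no | no |
| Month 3 (second laser) | no | no | yes |
| Month 6 (third laser) | yes | no | yes |
| 6 months after third laser | yes | yes | yes |

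The only post-baseline histology pair is in the last row. Someone withdrawn before it keeps usable scar assessments from whichever of Months 3 and 6 were reached, but no primary-endpoint pair. Someone kept in the study without a third laser has no date for the last row. For those treated on schedule, the windows put that visit between 5 + 5 = 10 and 7 + 7 = 14 months after the first laser, nominally at 12.

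**3. Possible bias of the retained-only estimate.** The protocol gives no SD, no effect size and no split of reasons for withdrawal, so everything in this step rests on assumptions. Let d be the share withdrawn and ρ the correlation between the tendency to be withdrawn and a poor laser-minus-control result, both taken as normal. In SDs of the paired difference,

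bias = ρ × φ(c) / (1 − d), where c is the (1 − d) normal quantile.

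For d = 0.20, c = 0.842 and φ(c) = 0.280, so the factor is 0.280 / 0.80 = 0.350. For d = 0.10, c = 1.282 and φ(c) = 0.1755, so the factor is 0.1755 / 0.90 = 0.195.

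| Assumed ρ | Bias, d = 0.20 | Coverage of 95% CI, d = 0.20 | Bias, d = 0.10 |
| --- | --- | --- | --- |
| -0.3 (against laser) | -0.105 | about 89% | -0.058 |
| 0 | 0 | about 95% | 0 |
| 0.3 | +0.105 | about 89% | +0.058 |
| 0.5 | +0.175 | about 76% | +0.097 |

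Coverage comes from 20,000 simulated trials of 60 with 12 removed, judged against the mean difference in all who were randomised.

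**4. Scale.** The 95% half-width for the mean paired difference is 1.96 / √48 = 0.283 SD with 48 pairs and 1.96 / √60 = 0.253 SD with all 60. At ρ = 0.5 the bias is 0.175 / 0.283 = 0.62 of the half-width.

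**5. Simple check.** If the withdrawn group's mean effect is g SD below that of the retained group, the bias is d × g. With d = 0.20, g = 0.5 gives +0.10, g = 0 gives 0 and g = -0.5 gives -0.10, which is the same order of size.

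**The case against.** The strongest reply is that nothing in 5.5 obliges anyone to remove a participant after a missed session. Withdrawal is optional and tied to being unable to continue, the bullets are examples, data already collected may be used, and 8.2 seeks full follow-up. Sections 5.5 and 7.2.3 are both permissive on pregnancy and can both be followed. Reasons for discontinuation are recorded, so removals can be told apart from other loss. The study is a descriptive pilot, and the handling of discontinuers is often left to the analysis plan.

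Much of this stands. A reader might infer that the withdrawal rule defeats the intention-to-treat analysis. The text does not support that: the rule opens a route to a completers' comparison without requiring it. The pregnancy passages are awkward together, not flatly contradictory. No type I error is at issue.

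A reader might also infer that the result must favour laser. That is plausible where removal follows a laser reaction. Section 7.1.1 lists pigment change, pain and itch as events to watch for, and the scar scales in 7.3.4 score the same features. But missed sessions may be unrelated to outcome, or may follow early improvement, which gives no bias or the opposite one. Nor need the whole 20% arise this way, since 8.1.1 allows it for drop-out and loss to follow-up in general.

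Two things remain. The aim of full follow-up supplies no final-visit date for someone without a third laser. And an analysis plan cannot restore a biopsy that was never taken.

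**Conclusion.** The point holds as an undermining of the intention-to-treat statement. Section 5.5 runs stopping laser and leaving the study together, 7.2.3 separates them, and 8.2 relies on their being separate. Because the primary endpoint, the final visit and the only post-baseline control biopsy all hang on the third laser, a participant withdrawn before that visit adds no post-baseline histology pair, and one kept in the study without a third laser has no date for it. These are facts of the text.

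Direction and size are not. If all of the planned 20% loss arose this way, 12 of 60 pairs would lack the primary endpoint, and the bias would lie between about -0.1 and +0.18 SD of the paired difference for assumed correlations of -0.3 to 0.5. It is zero if removal is unrelated to outcome, and smaller if fewer are removed. The harm falls on the estimates and the retention figure that feed the larger trial.

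**What to change.** - In 5.5, distinguish a participant who has stopped laser from one who has withdrawn from the study. State that stopping laser does not by itself end follow-up: both scars stay on the assessments already scheduled, where the participant agrees and the investigator sees no reason against it.
- Keep 6 months after the third laser as the final visit for those who receive it, so that the stated interval is unchanged. Add a fallback date for those who do not, for example Month 12 from the first laser, which 2.2.2 already uses. Moving everyone to that anchor is unnecessary: with the third laser at Month 6 give or take 30 days, Month 12 would fall about 5 to 7 months after it.
- In the retention figure, report withdrawals under 5.5 separately from other loss. The reasons are already recorded.
- Reconcile 5.5, 7.2.3, 7.5.6 and 8.2 with one another.

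This proposes no rule on when laser is stopped. It costs a short amendment and a few final visits of a kind already planned. Some of these participants may decline the final biopsy, so the histology pair is not guaranteed. Where all withdrawn participants are assessed, this source of bias disappears. The change has to come before the visits concerned, because missing biopsies cannot be recovered later.
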